### Background and rationale

1.1

There have been reports of an increase in food allergies for decades.^1^, ^2^ Currently, up to 10% of children worldwide suffer from IgE‐mediated food allergies^3^ with the most common being allergies to hen's eggs and cow's milk.^4^, ^5^ Additionally, of note are allergies to peanuts and tree nuts due to their association with severe allergic reactions and reduced spontaneous tolerance development.^3^

Allergies are attributed to a multi‐factorial pathogenesis. Multi‐gene traits and diverse environmental factors are regarded as key factors in shaping the development and/or severity of atopic entities.^6^, ^7^, ^8^, ^9^, ^10^, ^11^, ^12^, ^13^, ^14^

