#### Primary endpoint

2.4.1

This study will compare the diversity of the intestinal microbiome in infants with risk for atopic diseases in Group A versus Group B after the introduction of solids (time point V5). The diversity will be measured via alpha diversity calculations; the Shannon diversity, the Gini‐Simpson index, or the evenness will be calculated.^29^

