### Statistical methods

3.3

Diversity of the microbiome (primary endpoint) will be assessed utilizing alpha diversity calculations.^29^ The two study groups are compared using this diversity parameter. Moreover, based on the alpha diversity, other diversity indices like the Shannon diversity, the Gini‐Simpson index, or the evenness will be evaluated. No sample size calculation was performed due to the exploratory study design. *N* = 50 subjects per group is regarded as appropriate in order of magnitude of the few other studies in the context of pre‐chewing/saliva contact and/or microbiome analysis.^37^, ^38^, ^39^

In our explorative study, the primary efficacy analysis will be based on the full analysis set (FAS) and a secondary analysis will also be performed on the per protocol population (PPS) to assess the sensitivity of the analysis to the choice of analysis set. All safety analyses will be based on the full analysis set (FAS). The analysis will be performed without imputation of missing values. The significance level will be set to 0.05 (two‐sided). All other analyses will be considered explorative.

Univariable and multivariable logistic regression models will be performed for secondary binary endpoints (e.g., one diagnosed food allergy, food specific sensitisation, indices on microbiome diversity calculations). The analysis of secondary continuous endpoints (e.g., SCORAD, compliance over time) is conducted using analysis of covariance (ANCOVA). Child's sex, birth mode, number of siblings, pets, and other factors will be considered as covariates. Analysis will be carried out with the FAS. Based on the intention‐to‐treat (ITT) principle, the patients are analyzed according to the study group in which they started in.

Several explorative subcohort analyses (e.g., on antibiotic intake, infections) will be performed for the primary endpoint to find possible associations between covariates and diversity of the intestinal microbiome.

Selected secondary endpoints will also be analyzed with the PPS. The PPS is a subset of the FAS defined without participants with repeated insufficient consumption of the study product, defined as consumption <4 times/week (57%). As a general strategy, missing data will not be imputed in this study.

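### The diversity indices are listed as binary secondary endpoints for logistic regression, although they are continuous and the plan has an ANCOVA rule for such endpoints

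*Protocol article*

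**What the plan says.** All of this stands in the protocol article.

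- **Logistic rule (3.3 Statistical methods).** Besides univariable models, "multivariable logistic regression models will be performed for secondary binary endpoints (e.g., one diagnosed food allergy, food specific sensitisation, indices on microbiome diversity calculations").
- **Continuous rule (next sentence).** "The analysis of secondary continuous endpoints (e.g., SCORAD, compliance over time) is conducted using analysis of covariance (ANCOVA"). The diversity indices are not among its examples.
- **Covariates (3.3).** Sex, birth mode, number of siblings, pets and unspecified further factors are to be considered.
- **What the indices are (2.4.1 Primary endpoint).** "The diversity will be measured via alpha diversity calculations", with Shannon diversity, the Gini-Simpson index or evenness named as the measures. Sections 3.1.2 and 3.3 name the same three. None of these places gives a threshold.
- **Primary comparison (3.3).** "The two study groups are compared using this diversity parameter". No test or model is attached to it.
- **Size and level (3.3).** "No sample size calculation was performed due to the exploratory study design"; "50 subjects per group is regarded as appropriate"; "The significance level will be set to 0.05" (two-sided). Everything beyond the primary analysis is called explorative.
- **Food allergy rate.** The only figure is the general one in section 1.1, "up to 10% of children worldwide". No rate is given for infants with a family history of atopy.

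**The concern.** Logistic regression needs a two-valued outcome, and a Shannon, Gini-Simpson or evenness value is not one. Whoever carries out the rule must either set it aside or choose a threshold, possibly after seeing the data. A threshold discards information and makes the result depend on where it is placed. Diversity is the construct that the trial was built to study, so its secondary analyses deserve a rule that can be run.

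The same sentence raises a second, weaker question. It plans multivariable logistic regression for diagnosed food allergy in about 100 infants. If allergy is uncommon, few events would have to support a group effect and several covariates. Maximum-likelihood estimates may then be very imprecise or fail to exist because of separation.

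**Working it through.** **Plan's own figure.** There is none to reproduce: the article states no power, effect size, SD or expected number of events.

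**1. The two rules side by side.** Rule one: binary secondary endpoints, with diversity indices as an example, go to logistic regression. Rule two: continuous secondary endpoints go to ANCOVA. The indices are continuous by the article's own definition, so by type they belong under rule two, while by name they fall under rule one. Both cannot hold.

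**2. Cost if the indices were split at the median (assumption).** Inputs from the article: n = 50 per group, two-sided 5%. Assumed: normal data, equal SD, true difference d in SD units, no dropout. The effects 0.5 and 0.566 are illustrative; 0.566 is close to what 50 per group detects with about 80% power.

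Continuous analysis: power = Φ(d / √(2/50) − 1.96), where √(2/50) = 0.2.
- d = 0.5: Φ(2.50 − 1.96) = Φ(0.54) = 70.5%
- d = 0.566: Φ(2.83 − 1.96) = Φ(0.87) = 80.8%

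Median split: the proportions above the cut are Φ(d/2) and Φ(−d/2). Power = Φ((difference − 1.96·SE0) / SE1), with SE0 = √(2 × 0.5 × 0.5 / 50) = 0.100 and SE1 the unpooled standard error.
- d = 0.5: 0.599 v 0.401, difference 0.197, SE1 0.098: Φ(0.014) = 50.6%
- d = 0.566: 0.611 v 0.389, difference 0.223, SE1 0.0975: Φ(0.275) = 60.8%

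The loss is about 20 percentage points. The smallest difference with 80% power rises from 0.56 to 0.71 SD. Keeping 80% at 0.566 SD would take 78 per group instead of 50.

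The loss depends on the cut and the test. At 0.566 SD, cutting at the 25th percentile of one group gives 46%, and at the 10th percentile 27%. With a pooled-median split, simulation of the uncorrected chi-square test gives 67% (0.566 SD) and 57% (0.5 SD), but its true type I error is about 7.1%. Fisher's exact test gives 52% and 41%.

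**3. Food allergy: events per coefficient.** Group plus four named covariates makes 5 coefficients beside the intercept.
- 10% in both groups: 100 × 0.10 = 10 events; 10 / 5 = 2 per coefficient
- 10% v 5%: 50 × 0.10 + 50 × 0.05 = 7.5 events; 7.5 / 5 = 1.5 per coefficient

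A simulation (1,000 trials of 100 infants per scenario) checked each data set for complete or quasi-complete separation by linear programming. Trials with no event counted as not estimable. Assumed: male 50%, Caesarean 30%, pets 30%, siblings Poisson with mean 0.8 capped at 3, covariates unrelated to outcome, nothing missing.

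| Rate in Group B | Not estimable, no effect | Not estimable, risk halved in Group A |
|---|---|---|
| 3% | 74% | 86% |
| 5% | 46% | 68% |
| 10% | 12.5% | 27% |
| 15% | 2% | 9% |
| 20% | 0.2% | 2% |
| 30% | 0% | 0.3% |

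At 10% v 5%, 76% of the estimable fits checked had a 95% interval for the group odds ratio spanning more than a 20-fold range; at 10% in both groups it was 39%.

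**The case against.** **The split is not in the document.** This is right. The article states no dichotomisation. The phrase may be a drafting slip, and the full protocol or Appendix S1, neither shown, may define a category. A reader might infer that the trial will lose 20 points of power; the article does not support that, and the figures show only what one way of obeying the sentence would cost. What stands is that the indices are named as binary outcomes while defined as continuous. If it is a slip, it still needs correcting. Reading the indices as predictors does not fit a sentence that lists endpoints.

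**The primary comparison is untouched.** Also right. Because the primary endpoint uses the same indices, a reader might infer that it too goes to logistic regression. Section 3.3 assigns that method only to secondary endpoints.

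**The food allergy model may work.** A reader might infer that it will often be impossible to fit. The documents do not show this. The 10% is a worldwide figure for children in general. A cohort selected for family history could have more events, and at 20% failure is rare. In the other direction, the confirming food challenge is optional and missing values are not imputed, so confirmed events could be fewer. Covariates are only to be considered, not forced in, and a univariable model is also planned. The point therefore holds only as a caution tied to the event rate. It does not extend to sensitisation, for which no rate is given.

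**Conclusion.** The misclassification is certain from the text of section 3.3 and needs no outside source: continuous indices are assigned to a method for binary outcomes, against the article's own ANCOVA rule. The cost is conditional. With a median split, normal data and 50 per group, power would fall from about 71% to 51% at 0.5 SD and from about 81% to 61% at 0.566 SD.

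The sparse-event point is a conditional caution: about 2 events per coefficient if the rate is 10% and all four named covariates enter. At that rate 12.5% (no effect) to 27% (risk halved) of models would not be estimable, with far more failures at 5% or below and few at 20%.

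Severity is minor, because both parts concern secondary analyses that the plan calls explorative.

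**What to change.** 1. Delete the diversity indices from the examples of binary endpoints and place them under the existing ANCOVA rule for continuous secondary endpoints, transformed if skewed. Include the V1 value as a covariate where it exists. V5-solo infants have none, so a comparison that includes them must go without it.
2. If a dichotomised index is really intended, state the cut-point and its justification before the data are seen.
3. For food allergy, report the unadjusted risk difference with an exact or score confidence interval. If an adjusted estimate is wanted, use Firth-penalised logistic regression with group and one or two covariates named in advance.

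The first change costs one sentence and uses standard software. The third has a real price: fewer covariates mean less control of confounding in a comparison where parents choose the group, so the food allergy result should be presented as descriptive.

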#### Intervention description

2.3.1

Mothers of both groups will be encouraged to continue breastfeeding while weaning foods are introduced stepwise to the infant's diet. Parents will decide in advance which group they would like to join, and—depending on the child's individual development—when first complementary foods are to be introduced (Figure 1). All participants will be informed equally regarding current feeding recommendations.^17^, ^21^

All Group A participants will visit the study site at five timepoints (V1–V5). Group B participants will visit the study site at two timepoints (V1 and V5). Blood samples will be collected at V1 and V5; SPT will be performed at V5 only. Samples for microbiome analysis will be taken at indicated visits. Telephone calls are scheduled 2 weeks after V1, V2, V3, and V4 (Group A) and 2 weeks after V1 as well as one interim phone call at week 12 (Group B).

All caregivers will be encouraged to keep a weekly diary recording frequency of pre‐chewing, tolerability, and palatability of solids introduction, as well as any adverse events, concomitant medication, and diet.

V0 (collection of stools + skin swabs) and V6 (enhanced diagnostic in sensitized subjects, including oral food challenges) are optional.

V5 solo consists only of V5 (and optional V6); participants will not have been enrolled before.

Group A – “Interventional/Pre‐chewing Group”: The mother (or one other previously determined caregiver) of an eligible infant will receive a sugar‐free ground biscuit once the infant starts eating complementary foods. The biscuit is ground to ensure homogeneity of the amount of included food proteins. These amounts will be increased by a factor of five in four stages, each lasting 6 weeks ±14 days, V1–V4 (Table 2). The actual amount of total protein of the allergenic food in the first dose at V1 (Table 2) starts slightly below calculated discrete ED05 values for the correspondent food allergens,^25^ which are 2.1 mg peanut protein, 3.5 mg hazelnut protein, 2.3 mg hen's egg protein, and 2.4 mg cow's milk protein. Further ingredients of the biscuit are wheat flour type 550 and margarine processed with rapeseed oil.

**TABLE 2 pai70147-tbl-0002:** Content of Peanut, Hazelnut, Hen's Egg, and Cow's Milk protein in the ground biscuit.

Group A	Visit 1–Visit 2	Visit 2–Visit 3	Visit 3–Visit 4	Visit 4–Visit 5/6

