Group B – Non‐randomized reference: Solids will be introduced with reference to current feeding recommendations^17^, ^21^ based on the parents' decision but without pre‐chewing. Study participants will be invited for the end of study visit (V5) around the child's first birthday.

V5 solo consists only of V5 in Group B (and optional V6); participants will not have been enrolled before. This group serves as an additional reference group, as participants will not have been informed (biased) about premastication before.

At V1 and V5, blood samples from the infant will be collected and stored for allergy diagnostics (including food‐specific IgE and IgG4 to hen's egg, cow's milk, peanut, hazelnut, Ara h 2, Cor a 14, and wheat).

At V5 (or V5 solo), infants will be skin prick tested with hen's egg, cow's milk, hazelnut, and peanut.

In case of the detection of a food‐specific sensitization (elevated food‐specific IgE (>0.1 kU/L) or positive Skin Prick Test, SPT (wheel size >3 mm)) at V5, a double‐blind, placebo‐controlled oral food challenge (DBPCFC) will be offered for evaluation of clinical relevance (optional visit V6). Consequently, parents will be advised to continue feeding the study product until the DBPCFC is performed.

Importantly, apart from the intervention with the ground biscuit in group A, there are no further dietary restrictions imposed by the study protocol for both of the study groups.

All participants may continue their usual medications, as well as those taken for any concomitant diseases, including wheezing and eczema, throughout the study. All subjects who will undergo a DBPCFC will be advised to discontinue oral antihistamines 3–5 days before their appointment. For a detailed description of all study procedures, see Table 3.

**TABLE 3 pai70147-tbl-0003:** Schedule of Events: (a) Group A and (b) Group B.

Visit/Phone call	Enrolment/Screening		Intervention period							V5	(V6)^a^	Unscheduled visit^b^
	V0 (optional)	V1	PC 1	V2	PC2	V3	PC3	V4	PC4			
(a) *Schedule of Events – Group A*												
Timepoint (week)		0	2 wks after V1	6 wks (±14 d)	2 wks after V2	12 wks (±14 d)	2 wks after V3	18 wks (±14 d)	2 wks after V4	24 wks (±14d)		
Enrolment												
Informed consent	x	X^e^										
Check eligibility	x	X^e^										
Assessments												
Demographics/subject characteristics	x	x								x		
Family characteristics	x	x		x		x		x		x		
Medication, nutrition, exposure to smoking during pregnancy	x	x										

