#### Main secondary endpoints (for further endpoints, please see Appendix S1)

2.4.2

Compliance assessment/adherence of parents/caregivers conducting pre‐chewing via questionnaire on performance and frequency: query on a weekly basis, if performed daily; 4–7 times per week; <3 times/week (compliance defined as at least 4 days/week ≙ 57%)Composition of the oral microbiome and frequency of infant caries by 1 year of age (V5) according to the International Caries Detection and Assessment System (ICDAS, a clinical scoring system allowing detection and assessment of caries lesions and caries experience^30^)Frequency of IgE‐mediated food allergies to at least one of the four foods (hen's egg, cow's milk, peanut, hazelnut) after intervention by 1 year of age (V5) between Groups A and BAllergen‐specific IgE and IgG4 to hen's egg, cow's milk, peanut, hazelnut, Ara h 2, Cor a 14, and wheat at V1 and V5 in comparison between groups.Cumulative occurrence (frequency and severity) of respiratory and gastrointestinal infections (including oral infections) in comparison between groups

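### Weekly, categorical compliance in the pre-chewing group is assigned to ANCOVA as a continuous endpoint, a method that cannot validly analyse compliance over time

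*Protocol article*

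**What the plan says.** The statistical methods (section 3.3) sort secondary endpoints by type. Binary ones go to logistic regression. For the rest, "The analysis of secondary continuous endpoints (e.g., SCORAD, compliance over time) is conducted using analysis of covariance (ANCOVA"). Sex, birth mode, number of siblings, pets and other factors are to be considered as covariates, and every analysis other than the primary is called explorative.

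Compliance is the first of the main secondary endpoints in section 2.4.2: "Compliance assessment/adherence of parents/caregivers conducting pre‐chewing via questionnaire on performance and frequency". The recording scheme is "query on a weekly basis, if performed daily; 4–7 times per week; <3 times/week", with "compliance defined as at least 4 days/week".

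The intervention description (section 2.3.1) says "All caregivers will be encouraged to keep a weekly diary recording frequency of pre‐chewing". Group B introduces solids "based on the parents' decision but without pre‐chewing". In Table 3 the row for reviewing compliance with the study product appears only in the Group A schedule, where V5 falls at 24 weeks (±14 days).

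**The concern.** The method and the endpoint do not match in three respects.

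- **Scale.** What is recorded each week is an ordered category, or a yes/no value at the 4-day cut. It is not continuous. By the plan's own rule a yes/no endpoint belongs with logistic regression.
- **Repetition.** Compliance followed over time on a weekly query gives up to about 24 values per infant. Ordinary ANCOVA has one residual per row and nothing that links rows from the same infant.
- **Comparison.** Group B has no informative variation in pre-chewing frequency, even though its caregivers are also asked to keep the diary. There is no meaningful A-versus-B contrast. What can be examined is week or dose stage, and infant or family characteristics.

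The Discussion says that the trial will assess whether, when and how often premastication is practised. The uncertainty attached to the compliance results is therefore part of what the trial will report, although the endpoint is secondary.

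**Working it through.** The plan gives no error rate, power or sample size figure for this analysis, so there is none to reproduce. Its one related number checks: 4/7 = 57.1%, stated as 57%.

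**Inputs from the article:** 50 infants in Group A; weekly recording over about 24 weeks; two-sided 5% level; covariates that are constant within an infant.

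**Assumed, because the article gives no value:** intraclass correlation (ICC) of weekly compliance within an infant of 0.05, 0.2 or 0.5; equal (exchangeable) correlation between weeks; a null infant-level covariate split 25/25; all 24 weeks recorded.

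**Reading 1: weekly rows enter the ANCOVA (50 × 24 = 1,200 rows).**

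*Infant-level covariate.* Design effect DE = 1 + (24 − 1) × ICC. Actual type I error = 2 × [1 − Φ(1.96/√DE)].

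| ICC | DE | Type I error | Coverage of nominal 95% CI |
|---|---|---|---|
| 0.05 | 2.15 | 18.1% | 82% |
| 0.2 | 5.6 | 40.8% | 59% |
| 0.5 | 12.5 | 57.9% | 42% |

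Simulation with 2,000 replicates agrees. A normal outcome gives 17%, 41% and 62%. A yes/no outcome at an assumed 75% compliance gives 16%, 41% and 57%. A further simulation (4,000 replicates) with three ordered categories in assumed shares 20/40/40 gives 24%, 44%, 54% and 62% at latent ICC 0.1, 0.3, 0.5 and 0.7.

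*Week or stage effect.* This is a within-infant contrast. Its true variance is (1 − ICC) times the variance that the pooled model uses, so type I error = 2 × [1 − Φ(1.96/√(1 − ICC))]:

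- ICC 0.05: 1.96/√0.95 = 2.01, giving 4.4%
- ICC 0.2: 1.96/√0.8 = 2.19, giving 2.8%
- ICC 0.5: 1.96/√0.5 = 2.77, giving 0.6%

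The same model is thus too liberal for one kind of term and too conservative for the other. Other correlation structures could change the second result.

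**Reading 2: four stage values per infant.** DE = 1 + 3 × ICC = 1.15, 1.6 and 2.5, giving 6.8%, 12.1% and 21.5% for an infant-level covariate.

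**Reading 3: one value per infant**, such as the share of compliant weeks. Simulated type I error is 3.9% to 5.0% in the first simulation and 5.1% to 6.0% in the second, so close to nominal. This response holds no information on change over time.

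**The case against.** The strongest reply is that the article never says weekly rows are pooled. A reader might infer that about 24 correlated weeks per infant are treated as independent and that determinants of compliance will be declared far too often. The text does not support that as a statement of fact. It names no unit of analysis. It lists compliance beside SCORAD, which is also measured repeatedly in Group A and could reasonably enter as one V5 value. A per-infant percentage of compliant weeks would be continuous, would suit ANCOVA and would keep the error rate near 5%. No test of family characteristics as determinants of compliance is announced; the factors are named only as covariates. For a week effect, pooling would err towards caution under exchangeable correlation. The article is also abridged, and random effects or clustering are details that a full protocol or SAP commonly supplies.

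Most of this stands, and it makes the error rates conditional. It does not clear the sentence. The article has chosen a method and a variable type, and both disagree with its own definition of the endpoint. The reading that makes ANCOVA valid gives up the words over time, and the reading that keeps them gives wrong standard errors. Exploratory status relaxes the demand for multiplicity control. It does not make an interval with the wrong width acceptable.

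**Conclusion.** The point holds as a mismatch between a stated method and the endpoint it is assigned to. Plain ANCOVA cannot validly analyse weekly categorical compliance over time within Group A.

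The size depends on a choice that the article leaves open. With weekly rows, type I error is about 18% to 58% for infant-level covariates and about 4% down to under 1% for week or stage, under an assumed ICC of 0.05 to 0.5, exchangeable correlation, 50 infants and 24 complete weeks. With one value per infant there is essentially no inflation, but the time course is not analysed. It cannot be concluded that inflated false positives will occur.

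The consequence is limited to a secondary, exploratory endpoint. The primary comparison at V5 uses one value per infant and is not affected. The point is still worth acting on, because acceptance of premastication is among the things the trial sets out to assess and the correction costs almost nothing.

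**What to change.** In section 3.3, remove compliance over time from the examples in the ANCOVA sentence and add, for Group A only:

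- **Overall compliance** is the per-infant proportion of compliant weeks (at least 4 days, yes/no), summarised across infants with a 95% confidence interval based on infants.
- **Change over time** is analysed by logistic GEE, or by a mixed logistic model with a random infant effect, on weekly compliance yes/no, with week or dose stage as a fixed effect and standard errors clustered on infant.

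Keep ANCOVA for endpoints with one post-baseline value per infant, such as V5 SCORAD adjusted for V1 SCORAD.

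While editing, reconcile the weekly categories in section 2.4.2. Daily lies inside 4–7 times per week, and exactly 3 times per week falls in no category, so the yes/no value is not cleanly defined for every week.

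The cost is a sentence or two in the methods or SAP and slightly more analysis work. No new data, visits or participants are needed. Intervals for infant-level predictors will be wider than pooled rows would give.
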